## Abstract

**Background:**

About 80% of all stroke survivors have an upper limb paresis immediately after stroke, only about a third of whom (30 to 40%) regain some dexterity within six months following conventional treatment programs. Of late, however, two recently developed interventions - constraint-induced movement therapy (CIMT) and bilateral arm training with rhythmic auditory cueing (BATRAC) - have shown promising results in the treatment of upper limb paresis in chronic stroke patients. The ULTRA-stroke (acronym for Upper Limb TRaining After stroke) program was conceived to assess the effectiveness of these interventions in subacute stroke patients and to examine how the observed changes in sensori-motor functioning relate to changes in stroke recovery mechanisms associated with peripheral stiffness, interlimb interactions, and cortical inter- and intrahemispheric networks. The present paper describes the design of this single-blinded randomized clinical trial (RCT), which has recently started and will take several years to complete.

**Methods/Design:**

Sixty patients with a first ever stroke will be recruited. Patients will be stratified in terms of their remaining motor ability at the distal part of the arm (i.e., wrist and finger movements) and randomized over three intervention groups receiving modified CIMT, modified BATRAC, or an equally intensive (i.e., dose-matched) conventional treatment program for 6 weeks. Primary outcome variable is the score on the Action Research Arm test (ARAT), which will be assessed before, directly after, and 6 weeks after the intervention. During those test sessions all patients will also undergo measurements aimed at investigating the associated recovery mechanisms using haptic robots and magneto-encephalography (MEG).

**Discussion:**

ULTRA-stroke is a 3-year translational research program which aims (1) to assess the relative effectiveness of the three interventions, on a group level but also as a function of patient characteristics, and (2) to delineate the functional and neurophysiological changes that are induced by those interventions.

The outcome on the ARAT together with information about changes in the associated mechanisms will provide a better understanding of how specific therapies influence neurobiological changes, and which post-stroke conditions lend themselves to specific treatments.

**Trial Registration:**

The ULTRA-stroke program is registered at the Netherlands Trial Register (NTR, http://www.trialregister.nl, number NTR1665).

## Background

In the Netherlands, each year more than 32,000 patients sustain a stroke [1,2], and the incidence is expected to have increased by 30-45% by 2015 [3]. About 80% of stroke survivors suffer from an upper limb paresis immediately after stroke [4], hampering movement of the paretic arm and bimanual coordination [5].

Spontaneous recovery after stroke is limited, and knowledge about which mechanisms lead to spontaneous recovery is incomplete [6]. Restitution of non-infarcted penumbral tissue (i.e., reestablishment of metabolism in the tissues surrounding the infarcted area) [7] and resolution of diaschisis (i.e., relief of suppression of anatomically related brain areas) [8], together with recovery of neurotransmission in spared tissue near and remote from the infarct [7,8], are held mainly responsible for the nonlinear recovery pattern observed in the first weeks post-stroke [6].

In addition to these early post-stroke developments, functional recovery of the upper extremity is promoted by plastic changes in the functioning of the brain, which, in general, also occur in learning [9]. These experience-induced changes are brought about by a combination of neural repair and neuro-anatomic reorganization, and include greater excitability and recruitment of the neurons in both hemispheres, sprouting of dendrites, and strengthening of synaptic connections [7,10-16].

Although the aforementioned processes may suggest an optimistic view on post-stroke recovery, only one third of all stroke patients regain some dexterity within six months using conventional treatment programs [7]. This means that 60-70% of all stroke survivors will continue to experience major functional limitations of the upper extremity [17], which are associated with diminished health-related quality of life after stroke [7,18].

In light of this grim prospect, it is encouraging that recent studies, capitalizing on the concept of experience-induced neuroplasticity, have produced promising results using specific interventions aimed at arm-function improvement. One such intervention is bilateral arm training with rhythmic auditory cueing (BATRAC), which has been shown to have beneficial effects on the paretic arm in chronic stroke patients [19], possibly as a result of changes in contralesional cortical networks [20]. This suggests that motor function in the impaired paretic arm may be regained by exploiting interhemispheric interactions [21]. In particular, based on the principle of interhemispheric recruitment from the non-affected hemisphere (i.e., exercise-induced neuroplasticity by means of "neural cross-talk"), BATRAC may serve as an effective therapy for patients in whom the corticospinal tract (CST) system is seriously affected [22] - a group of patients for which effective therapies are urgently lacking and prospects of arm function recovery are particularly poor [8,17]. Furthermore, a recent meta-analysis on upper limb robotics suggests that distally oriented repetitive bilateral arm training is more effective than a more proximally oriented approach [23]. In addition, longitudinal studies with repeated measurements in time suggest that an early return of wrist and finger extension is a pre-requisite for regaining some dexterity [24-26]. These findings support the hypothesis that the effectiveness of BATRAC may be enhanced by performing repetitive flexion and extension movements of wrist and fingers, rather than rhythmic movements of more proximal parts of the arm.

In contrast, various controlled trials have suggested that intensive unilateral training by constraining movements of the non-paretic arm (constrained-induced movement therapy, CIMT) is an effective method for improving upper limb function in chronic stroke patients [18,27-29]. This suggests that training may also induce beneficial changes in the affected rather than the non-affected hemisphere and raises the question whether the improved functionality of the paretic arm with BATRAC indeed results from exploiting interhemispheric interactions, or merely from training with the affected arm [20].

The ULTRA-stroke program entails a randomized clinical trial (RCT) in which the merits of both BATRAC and CIMT are compared with each other and those of an equally intensive (i.e., dose-matched) conventional treatment program. To this end, participants will be divided over three intervention groups and the effects of the interventions will be assessed prior to training (t0), after 6 weeks of training (t1), and 6 weeks after training (t2). The primary aim of the ULTRA-stroke program is to assess the relative effectiveness of the three interventions on a group level and as a function of patient characteristics. In addition, the program aims for delineating the functional and neurophysiological changes that are induced by those interventions. This led to the following research questions:

▪ Which of the three interventions - modified BATRAC, modified CIMT, or a dose-matched conventional treatment (DMCT) - is more effective in terms of recovery of (unimanual and bimanual) hand and arm function in subacute stroke patients?

▪ How are the observed changes in functionality related to changes in peripheral stiffness, interlimb interactions, and cortical inter- and intrahemispheric networks?

The effectiveness will be assessed by a range of functional outcome measures pertaining to motor ability of the paretic arm, activities of daily living (ADLs), bimanual coordination, and peripheral motor functioning. Besides further elucidating the merits of bilateral versus unilateral upper limb training in general, the study will generate specific insights into the effectiveness of distally oriented (modified) BATRAC, specifically aimed at improving wrist and finger extension [24-26], and into the effectiveness of (modified) CIMT as applied in a thus far hardly studied stage after stroke [30].

In light of contrasting results and divergent perspectives regarding underlying mechanisms of current interventions [31], their potential dependence on the neurological characteristics of stroke survivors will also be a topic of investigation in the ULTRA-stroke program. It has been proposed that the effectiveness of CIMT is dependent on CST integrity [32-34], which is essential for motor control of the distal part of the upper limb. On the other hand, BATRAC may be expected to be less dependent on the integrity of the CST, as it appears to induce reorganizations in cortical inter- and intrahemispheric networks [21,22]. To cope with this issue, participants will be categorized in terms of their motor ability of the distal part of the arm [8].

In short, we hypothesize that both modified CIMT and modified BATRAC significantly improve upper limb function when compared to DMCT. Modified CIMT is expected to have a larger impact on those subjects who already showed some dexterity at recruitment than on subjects that were more restricted in this regard, given the proposed importance of CST integrity for motor control of the distal part of the upper limb [25]. Modified BATRAC, on the other hand, is expected to be also effective for the latter group of subjects, thanks to influences stemming from and reorganizations in the contralesional hemisphere (see also [35-37]). The effects of modified BATRAC and modified CIMT are both expected to sustain during the follow-up period of 6 weeks. To uncover the mechanisms associated with intervention-induced functional improvement, three kinds of analysis will be included.

First, endpoint mechanical behavior of the paretic wrist, under both passive and active conditions, will be assessed to determine both paresis and stiffness, the latter described in terms of intrinsic visco-elasticity and reflexive feedback properties [38]. In *active *posture tasks the negative signs of post-stroke limb dysfunction prevail (viz., paresis and poor adaptation of reflexes; [39]). Under *passive *conditions, however, enhanced joint stiffness and hyper-excitability of the reflex loop (viz. enhanced tendency for synchronous and self-sustained firing of the motor neuron pool) are evident [40,41]. Because the spinal reflex loop is under control of higher brain areas, loss of CST integrity and persistent central nervous system reorganization is anticipated to be related to high joint stiffness, absence of reflex modulation, and signs of hyper-excitability of the reflex loop. Assuming that increased joint stiffness is specifically associated with loss of CST integrity, modified BATRAC is expected to be more effective in reducing these effects than modified CIMT for participants with minimal hand/finger control.

Second, bimanual coordination will be examined in all detail. Bimanual coordination is characterized by interlimb interactions [42,43] that result in stabilization of specific bimanual coordination patterns [5,44-49]. The success of bilateral training protocols (such as BATRAC) has been ascribed to the presence of such interlimb interactions [21], suggesting that influences from the contralesional hemisphere are beneficial for performance of the paretic limb. Bilateral training may also induce adaptations in these interactions, potentially strengthening its advantageous influence on paretic arm performance as well as improving bimanual performance. Therefore, modified BATRAC is expected to induce more improvement in these interactions than both modified CIMT and DMCT.

Third, treatment-induced neuronal reorganization will be identified using magneto-encephalographic recordings (MEG). Given its high temporal resolution, MEG is a very suitable non-invasive tool for studying patterns of correlated neuro-electrical activity within and across hemispheres. MEG recordings of unimanual and bimanual tasks will be conducted prior to and after interventions to investigate treatment induced changes in these patterns.

Functional MRI studies and TMS studies already indicated that, during paretic arm movement, CIMT results in increased metabolic activation in the primary sensorimotor cortex of the affected hemisphere [50-62], whereas BATRAC results in increased metabolic activation in the contralesional cerebrum and ipsilesional cerebellum [20,21].

Modified CIMT is hence expected to result primarily in changes in ipsilesional hemisphere functioning, i.e., greater activity in the primary sensorimotor cortex of the affected hemisphere and increased phase synchronization between regions surrounding the lesion (we note that assessing the latter requires the high temporal resolution of encephalographic recordings), which may be related to restitution of its former functionality. In contrast, modified BATRAC is expected to primarily induce adaptations in the contralesional hemisphere, enhanced activity in the (ipsilesional) cerebellum (possibly reflecting enhanced timing abilities), and a considerably greater increase in the degree of phase synchronization between the lesioned hemisphere and the contralesional hemisphere than will occur as a result of either modified CIMT or DMCT. This finding would indicate compensatory cortical reorganizations in which the coupling to the nonaffected hemisphere acquires a special role in the motor control of the paretic arm.

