### Design

The intake procedure will take place the week following informed consent. After the intake procedure, which will include the first assessment of outcome variables, patients will be stratified in those with some dexterity and those with minimal control of paretic wrist and finger extension. Patients with some dexterity are able to execute > 10° finger extension of each metacarpophalangeal and interphalangeal joint of all digits and > 20° wrist extension. Patients with minimal control are those who meet the criteria of inclusion (i.e., able to execute at least 10° of active wrist extension, at least 10° of thumb abduction/extension, and at least 10° extension in at least 2 additional digits), but not (yet) the criteria of some dexterity. After stratification, patients will be randomized in permuted blocks and allocated to one of the three intervention groups (i.e., modified BATRAC, modified CIMT, or DMCT). Concealed allocation is effectuated with an online, computerized randomization procedure according to the minimization method [65]. Other therapists and social workers will provide regular care depending on patient needs.

After the first assessment and randomization, an intervention period will take place for 6 consecutive weeks. The effects of the interventions are examined using a pretest-posttest design. The pretests (t0) are performed in the week prior to intervention and posttests (t1) are performed in the week after intervention. The degrees to which changes are sustained are examined using retention tests (t2), 6 weeks after completion of the intervention. Figure 1 shows the time schedule for effectuating the entire protocol. (Figure 1.)

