### Outcome variables

The primary outcome variable will be the score on the Action Research Arm test (ARAT). Secondary outcome variables are the scores on the Motricity Index (MI) of the arm, Fugl-Meyer for the arm (FM-arm), Nine Hole Peg test (NHPT), Erasmus modification of the Nottingham Sensory Assessment (EmNSA), Motor Activity Log (MAL), and Stroke Impact Scale (SIS version 3.0). All assessments will be applied to all patients at t0, t1, and t2.

Non-parametric statistics for independent samples will be used [81]. A Kruskal-Wallis test will be used to examine whether improvements before and after intervention (from t0 to t1) were significantly different between the three intervention groups (i.e., BATRAC, CIMT, and DMCT). When a significant difference is found between the three groups, a *post-hoc *Mann-Whitney U test will be applied to reveal which groups (CIMT, BATRAC, or DMCT) differ significantly from each other. The same procedure will be used for observed changes after the 6 weeks retention period, i.e., from t1 to t2.

The ARAT is a valid, reliable, and responsive performance test [82] of the ability to perform gross movements and to grasp, move, and release objects differing in size, weight, and shape [83]. The minimal clinically important difference is set at about 10% of the scale's range, i.e., 6 points [84]; improvement by > 10 points is defined as return of dexterity [17].

The MI will be used to measure strength in upper extremities [85]. Higher scores represent greater strength in the upper limb. This instrument provides a reliable and valid assessment of the presence of paresis in stroke patients by testing 6 functions rated for each limb [64,85].

The FM arm score is a reliable and valid motor performance test consisting of 33 tasks performed by the affected upper limb [86,87]. The FM-arm test evaluates the ability to make movements outside the synergistic pattern. Performance on each task is rated as 0, 1, or 2, with higher rates representing better performance. The FM-arm measure will be used as the sum of 33 ratings (possible range 0 to 66 points).

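### Part of the primary aim is how treatment effects vary with patient characteristics, but the stated ARAT tests compare treatment groups only and cannot estimate or test a treatment-by-stratum difference

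*Protocol article*

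**What the plan says.** The Background section of the protocol article gives a primary aim with two parts: to "assess the relative effectiveness of the three interventions on a group level and as a function of patient characteristics". The Discussion paragraph of the Abstract repeats both parts.

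The hypotheses, also in the Background, come in three pieces:
- The lead hypothesis is at group level: "we hypothesize that both modified CIMT and modified BATRAC significantly improve upper limb function when compared to DMCT".
- The second concerns effect modification: "Modified CIMT is expected to have a larger impact on those subjects who already showed some dexterity at recruitment", compared with patients who are more restricted.
- The third concerns BATRAC in the more restricted patients: it "is expected to be also effective for the latter group of subjects".

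The Design section builds the factor into the trial: "patients will be stratified in those with some dexterity and those with minimal control of paretic wrist and finger extension", before allocation to the three arms.

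Under Outcome variables, the ARAT is named as the primary outcome and the general approach is fixed: "Non-parametric statistics for independent samples will be used". A Kruskal-Wallis test asks whether improvements from t0 to t1 "were significantly different between the three intervention groups (i.e., BATRAC, CIMT, and DMCT". If it is significant, pairwise Mann-Whitney tests follow. The same procedure is repeated for t1 to t2. The stratum is not mentioned there. It does appear as a factor under Peripheral stiffness, in the repeated measures analysis of the wrist measures.

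**The concern.** A Kruskal-Wallis test on three treatment groups pools the two dexterity strata within each arm. Its result, and that of the pairwise follow-up tests, says whether the arms differ overall. It does not say whether CIMT gains more over DMCT in one stratum than in the other. The part of the primary aim about patient characteristics, and the CIMT hypothesis that makes it specific, therefore have no matching ARAT analysis.

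What is at stake is the claim about who benefits from which therapy. The Discussion expects the trial results, together with the mechanism findings, to help clinicians choose a therapy and fit it to the individual patient. A pooled comparison cannot supply the ARAT evidence for that. Without a stated estimate and its uncertainty, readers would have no measure of how little about 10 patients per cell can show.

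**Working it through.** **1. The plan's own sample size.** Inputs from Power analysis: squared sum of normal quantiles 10.43 (alpha 0.017, power 80%), variance 26, squared difference 36, ratio 1.

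n per group = 2 × 10.43 × 26 / 36 = 15.07, against the stated 15. With 25% drop-out, 15 / 0.75 = 20 per arm, or 60 in total. The figure reproduces. It is sized for a pairwise difference between arms, not for a difference between strata.

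**2. What the pooled test can see.** This was checked by simulation under assumed conditions: normal outcomes, SD 5.1 (the square root of 26), 20 per arm, equal strata, one active arm, Kruskal-Wallis at 0.05, 4,000 trials per scenario.

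| Effect in stratum 1 / stratum 2 | Average effect | Trials rejecting |
|---|---|---|
| +6 / +6 | +6 | 96% |
| +12 / 0 | +6 | 77% |
| +6 / −6 | 0 | about 1% |

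A significant result is likely both when effects are equal and when all the benefit lies in one stratum. Opposite effects go unseen. The result does not tell these situations apart.

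**3. Precision of a treatment-by-stratum contrast.** The contrast is the CIMT-DMCT difference in one stratum minus the same difference in the other, which uses four cells.

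Cell size with equal strata (assumed; the article gives no split): 20 / 2 = 10. After 15% drop-out it is 8.5, and after 25% it is 7.5. Power analysis mentions both drop-out rates.

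SE = √(4 × 26 / n per cell). Detectable size at 80% power and two-sided 0.05 = (1.96 + 0.84) × SE = 2.80 × SE. Power for 6 points = Φ(6/SE − z), with z = 1.96 at 0.05 and 2.39 at 0.017.

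| n per cell | SE | Detectable size (0.05) | Power for 6 points, 0.05 | Power for 6 points, 0.017 |
|---|---|---|---|---|
| 10 | 3.22 | 9.03 | 46% | 30% |
| 8.5 | 3.50 | 9.80 | 40% | 25% |
| 7.5 | 3.72 | 10.43 | 36% | 22% |

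**4. Unequal strata.** With a 30/70 split, Var = 2 × 26 × [1/(0.3n) + 1/(0.7n)], where n is patients per arm. For 20 per arm, power for 6 points is 40% at 0.05 and 25% at 0.017. For 15 per arm it is 31% and 18%.

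**5. Size needed.** For 80% power on a 6-point between-stratum difference with equal strata: 46 per arm at 0.05, or 61 at 0.017. The 6-point size is borrowed from the plan's minimal important difference; the article states no size for the interaction.

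**6. Within-stratum comparison.** This is the form that the BATRAC statement takes. For a 6-point difference at alpha 0.017, power is about 60% with 10 per cell and 46% with 7.5.

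**The case against.** The strongest reply is that this is a condensed article. It gives the main between-group tests and does not rule out further ARAT analyses. Subgroup models are often left to a full protocol or analysis plan, and the stratum's appearance under Peripheral stiffness shows that the authors had it in mind. This stands in part. One cannot say that the trial is unable to answer the question, only that the stated ARAT method does not. It does not remove the point, because the article does choose the primary-outcome tests, and the tests chosen leave out part of the aim.

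Three stronger readings are tempting, and the documents support none of them:
- **That the primary aim as a whole is about differences between strata.** The aim puts the group level first, the effectiveness research question is at group level, and the lead hypothesis is a main effect. The stated tests address all of these.
- **That the BATRAC statement is also an interaction hypothesis.** It says that BATRAC should work in the more restricted patients too. A within-stratum comparison with DMCT would address that directly. Only the CIMT statement is clearly about effect modification.
- **That the authors plan to run the tests in each stratum and compare which are significant.** No such analysis is described.

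The figures are also conditional. The article labels 26 as the expected variance of the ARAT, without saying that it applies within strata or to change. The 9 to 10.4 points belong to a single contrast at 0.05 and should not be attached to a joint two-degree-of-freedom interaction test. Finally, the Discussion's promise to clinicians rests jointly on mechanism findings, not on subgroup ARAT results alone.

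**Conclusion.** The point holds in this limited form. The group-level part of the aim is covered. The part on patient characteristics, and the CIMT-by-dexterity hypothesis, have no ARAT analysis that can estimate or test them.

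That mismatch follows from the text and needs no numerical assumption. The precision figures do need assumptions: within-cell variance 26, equal strata, a normal approximation and 7.5 to 10 patients per cell. On that basis only very large between-stratum differences, about 9 to 10.4 points on one contrast, would be detected with 80% power. A 6-point difference would more often be missed than found. Any such analysis at this sample size is exploratory estimation.

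**What to change.** Keep the Kruskal-Wallis and Mann-Whitney tests for the group-level comparison. Add one pre-specified supplementary model for the ARAT at t1, with baseline ARAT, arm, stratum and arm-by-stratum as terms. No such model is in the article now, so it has to be written in as an addition.

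From this model, report with confidence intervals:
- the CIMT-DMCT and BATRAC-DMCT differences within each stratum;
- the between-stratum difference in each of these two contrasts.

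Label the analysis exploratory. State that significance in one stratum only is not evidence of a difference between strata. State the precision: SE 3.2 to 3.7 points and detectable size about 9 to 10.4 points for a single contrast at two-sided 0.05, with the assumptions above. Moderate the Discussion's wording on choosing therapies for individual patients accordingly.

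The cost is one additional model, its description and a weaker stated claim. The stratum and the ARAT are already recorded, so no new patients or measurements are needed.
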